### Statistical methods

Case–control study analyses will be conducted using conditional logistic regression. Matching factors (i.e. age, area and year of first invitation to bowel cancer screening) are controlled for in design, and additional analyses will be stratified by sex and anatomical subsite. All statistical analyses will be performed using the statistical software STATA version 12 and/or R version 2.13.0.

The ***primary objective*** of this case–control will be to assess the effect of various measures of participation in bowel cancer screening *strictly prior to* the case’s date of *index/first diagnosis* on incidence from advanced stage primary CRC (see details in Table 1). The primary measure of participation to screening will be whether an individual ever attended at least one screen episode prior to diagnosis. Secondary measures will be the total number of screens, the time since last screen, the time since penultimate screen, the interval between last screen and penultimate screen, the maximum interval between 2 screens, the average interval between 2 screens, the total number of invitations, the patient's age at first screen, and the patient’s age at last screen.

‘Time since last screen’ will give estimates of the likely benefit of screening at different intervals. It will include whether that time span fell within the past two years, as this corresponds to the NHS BCSP interval and approximates the estimated preclinical screen-detectable period (PCDP).

***The secondary objective*** will be to consider the effect of screening on overall CRC incidence, regardless of stage. Similar measures of participation will be used.

*Self-selection* and *exposure opportunity* biases will be addressed using the methods described in the *Bias & Effect modification* section.

Secondary analyses will consider time since last screen stratified by age at diagnosis/pseudo-diagnosis, by *index/first tumour* detection mode, and by region (Main phase only). Analysis may be adjusted for stage at diagnosis. The effect of attending a screen in a particular 5-year age band (e.g. 60–64), in the pilot phase, or 2-year age band (e.g. 60–61), in the main phase, on incidence from advanced stage primary CRC in the subsequent 5-year age band (i.e. 62–66 or 65–69, respectively) will also be investigated, as performed for the cervical screening audit [17]. The results of this analysis should be very similar to those obtained from the analysis of ‘time since last screen’ after stratifying the analysis by age at diagnosis/pseudo-diagnosis.

In the main phase of the study, the effect of invitation to bowel screening and attendance at screening prior to the *index screen* of the case will also be assessed among screen-detected cases matched to controls screened within the same screening interval (Table 1 Design 5).

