## Methods/Design

### Study design & objectives

The study will be a matched comparison of recently diagnosed/incident advanced stage primary CRC (colon, rectosigmoid junction and rectum) cases with general population controls free of advanced stage disease, with respect to screening exposure strictly prior to the case's date of *index/first diagnosis* (set as pseudo-diagnosis date in controls). There will be two controls per case.

The primary objective will be to determine whether the event of having been screened prior to diagnosis is superior to not having been screened in terms of incidence of advanced stage primary CRC. In addition, we plan to assess the benefit by time since last negative screen and number of screens among other measures of exposure. The secondary objective will be to consider the effect of screening on overall CRC incidence, regardless of stage.

A methodological objective of this protocol is to apply a procedure using data from RCTs and from other cancer screening programmes, in this case, from the cervical (NHS CSP) and the breast (NHS BSP) screening programmes, to adjust the analysis of the case–control studies for self-selection bias.

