#### Exposure opportunity (frequency) bias

Once diagnosed with cancer, the cases come under clinical management and do not continue with routine screening as before. The controls, however, will continue to attend screening. To avoid a potential bias *in favour* of screening, controls are given a pseudo-diagnosis date that is the same as that of their matched case and screening history is only considered up to that date [29].

In contrast, the fact of the case having necessarily a diagnosis of cancer and a control usually not having such a diagnosis, induces an artificially higher retrospective probability of screening exposure in the cases, a bias *against screening* (i.e. the screen-detected cases will always have this screen recorded at diagnosis, whereas the large majority of controls will not at pseudo-diagnosis date). Simply excluding the detection screens of the cases from the histories would bias the results *in favour* of screening. A driver of this bias is prevalence screening and, as the NHS BCSP is a relatively young programme with at most 3 rounds at the planned start of the pilot phase (January 2012), this bias may initially be present although it is likely to decrease for subsequent evaluations.

The extent of screening opportunity bias will be investigated first, by applying an analytical correction to the odds ratio using the method developed by Duffy and collaborators [30], and second, by performing sensitivity analyses in which the date of pseudo-diagnosis for controls whose matched cases have had a screen-detected *index diagnosis* will be extended by up to 3 years, the estimated average sojourn time for each screen-detected case, to counteract the artificially higher retrospective probability of screening exposure in cases [29]. A shorter sojourn time may however be more appropriate for screen-detected tumours of stage Duke B or worse [31].

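### The interval objective is set on time since last negative screen, but the analysis uses time since last screen, which counts the detection screen and distorts the by-interval odds ratios

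*Protocol article*

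**What the plan says.** The section Study design & objectives states: "we plan to assess the benefit by time since last negative screen and number of screens among other measures of exposure".

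The Statistical methods section names different variables: "Secondary measures will be the total number of screens, the time since last screen, the time since penultimate screen", followed by several interval, age and invitation measures. None is restricted to negative screens. Time since last screen is the variable that "will give estimates of the likely benefit of screening at different intervals". One band is named for it: "It will include whether that time span fell within the past two years", chosen because it matches the programme interval. The same variable is then carried into secondary analyses stratified by age, detection mode and, in the main phase, region.

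The section on exposure opportunity bias confirms that the detection screen stays in the case's history: "the screen-detected cases will always have this screen recorded at diagnosis, whereas the large majority of controls will not at pseudo-diagnosis date". It calls this a bias against screening and explains why the obvious remedy is not used: "Simply excluding the detection screens of the cases from the histories would bias the results" in favour of screening. It plans a correction to the odds ratio, an extension of the controls' pseudo-diagnosis date by up to 3 years, and an analysis of screen-detected cases with the index screen excluded. Table 1 gives the related Design 5.

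**The concern.** The two variables agree for anyone whose last screen was negative. They differ for screen-detected cases. For these, the last screen is normally the detection screen, shortly before diagnosis, while the last negative screen is an earlier one or does not exist. Controls' last screens are not tied to a diagnosis in this way.

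The recent band therefore gains cases because of how they were found, and the older band loses them. The ever-screened total does not change, but its division by recency does. An odds ratio by time since last screen then mixes the protection left by an earlier negative test with the act of detection. This analysis is secondary, but it is the one meant to inform the screening interval.

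**Working it through.** **1. Where the mechanism applies (Table 1).** Designs 2 to 4 count exposure up to the index diagnosis, so the detection screen is included. Design 1 counts it up to the first diagnosis, which is the same date for cases with no previous diagnosis. The mechanism does not apply as described to Design 1 cases with a previous diagnosis, or to the analysis that excludes the index screen.

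**2. The plan's own figures (Power calculation, Table 3).** The matched odds ratio is 16/20 = 0.80. The odds ratio from the margins, with 55% of cases and 59% of controls ever screened, is (0.55/0.45)/(0.59/0.41) = 0.85. The margins are used below because the bands divide them.

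**3. Effect on the bands.** Let s be the share of cases that are screen-detected and f the share of all other attenders whose last screen was within two years. The document gives neither, so both are assumed. Ever-screened totals stay at 55% and 59%.

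- Cases, within 2 years: s + f(0.55 − s). Cases, beyond: (1 − f)(0.55 − s). Never: 0.45.
- Controls, within 2 years: 0.59f. Controls, beyond: 0.59(1 − f). Never: 0.41.
- Each odds ratio is against never screened.

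With f = 1 (all last screens within two years), the case share is s + (0.55 − s) = 0.55 for any s, so the within-two-years odds ratio is 0.85 and is not affected.

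With f = 0.7, the control shares are 0.413 and 0.177:

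| s | Cases ≤2 y | OR ≤2 y | Cases >2 y | OR >2 y |
|---|---|---|---|---|
| no distortion | 0.385 | 0.85 | 0.165 | 0.85 |
| 10% | 0.415 | 0.92 | 0.135 | 0.69 |
| 20% | 0.445 | 0.98 | 0.105 | 0.54 |
| 30% | 0.475 | 1.05 | 0.075 | 0.39 |

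For example, at s = 10%: (0.415/0.45)/(0.413/0.41) = 0.92 and (0.135/0.45)/(0.177/0.41) = 0.69. The row without distortion assumes that all case attenders' last screens are spread as the controls' are.

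**4. Check under no true effect.** A simulation of three biennial rounds let screening have no effect on who becomes a case. Assumed inputs were test sensitivity 0.3 to 0.5, mean sojourn 2 to 3 years, and mixed attendance with about 44% of controls never screened. Between 12% and 24% of cases were then screen-detected, all of them in the recent band. A sound measure would give 1 in both bands.

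| Measure | OR ≤2 y | OR >2 y |
|---|---|---|
| Time since last screen, as planned | 1.03–1.11 | 0.79–0.91 |
| Non-screen-detected stratum | 0.55–0.77 | 0.83–0.93 |
| Detection screen dropped from cases only | 0.51–0.74 | 1.64–2.18 |

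**5. The planned remedies against the stated objective.**

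- *Odds-ratio correction:* no version for each time band is stated.
- *Date extension:* it also moves the point from which the controls' time since screen is counted.
- *Detection-mode strata:* every screen-detected case has a recent last screen, so that stratum has no never-screened cases to contrast. The other stratum favours screening (step 4).
- *Time since penultimate screen:* it steps back to the right screen in a screen-detected case but one screen too far in controls.
- *Adjusting for screen-detection (Designs 1 and 2):* controls without cancer have no detection mode.
- *Screen-detected analysis and Design 5:* these treat the index screen alike in cases and controls, but are described for prior attendance or invitation, not for time bands.

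**The case against.** The strongest reply is that the protocol already knows of the problem. It names the asymmetry, gives its direction, explains why detection screens cannot simply be removed, and plans a correction, a sensitivity analysis, detection-mode strata and a design without the index screen. The measure is secondary, and exact exposure coding is often left to a fuller document. Much of this stands: the bias is not overlooked. What remains is that the methods fix a different variable from the objective and present it as giving benefit by interval.

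A reader might infer that recent screening would be made to look harmful. With last screens spread evenly over two years and 10% to 30% of cases screen-detected, the odds ratio against never is about 1.3 to 2.2 for a six-month band and 1.9 to 4.1 for a three-month band. The protocol names neither band and gives no screen-detected share. In its only named band, the same assumptions leave 0.85 unchanged. The supported statement is relative: recent screening looks less protective than it should compared with older screening.

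A reader might also infer that restricting to non-screen-detected sets would cure this. It would not: that stratum gave 0.55 to 0.77 in the recent band under no effect, further from 1 than the planned measure.

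**Conclusion.** The objective and the methods name different interval variables, and the one analysed places screen-detected cases in the recent band in Designs 2 to 4 and for Design 1 cases with no previous diagnosis. The by-interval pattern is distorted, and no planned remedy is stated to deliver the promised estimate.

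The direction is firmer than the size. The distortion across the two-year boundary is nil if all last screens fall within two years, moderate in the null simulation, and larger under the 70% assumption with 20% to 30% of cases screen-detected. Some last screens beyond two years are likely, since routine invitation stops at 74 while cases run to age 89, but the document does not give the spread. The primary ever-screened measure does not use this variable.

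**What to change.** Reconcile Study design & objectives with Statistical methods by adding time since last negative screen as the interval measure.

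- Estimate it in the planned screen-detected analysis (the Design 5 type), with the index screen removed from both the case and its matched controls screened in the same period. Add a version restricted to Duke B+ cases, because Table 1 defines Design 5 for Duke A to D.
- Keep time since last screen as a descriptive measure. State that its recent band contains the detection screens, and do not interpret it alone as benefit by interval.
- Label any non-screen-detected stratum as biased in favour of screening and do not read it alone.
- Do not drop the detection screen from cases only.

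The cost is some wording, a little more analysis, and fewer informative sets in the short bands. The planned variables already include every screening episode, its date and end code, and the tumour detection mode.

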**Design 1**			
	Previous diagnosis	None	None
		CRA	CRA
		Duke A CRC	Duke A CRC
	Index diagnosis	Duke B+ CRC	_
	Analysis	Exposure to screening prior to *first diagnosis* of case	
		Controlling for previous history of CRA & CRC	
		Adjusting for screen-detection of CRC	

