**Design 5**			
	Previous diagnosis	None	None
		CRA	CRA
	Index diagnosis	Any CRC (Duke A-D)	_
		Screen-detected	Last screened in same year as case index screen
	Analysis	Exposure to screening prior to *index diagnosis* of case	
		Controlling for previous history of CRA	

CRA: Colorectal Adenoma; CRC: Colorectal Cancer.

Duke A CRC: CRC diagnosed at stage Duke A; Duke B+ CRC: CRC diagnosed at stage Duke B, C or D.

Matched general population controls will be restricted to those individuals who have never had stage B or worse primary CRC, but may have had early stage primary CRC (Duke’s stage A) or CRA prior to and including the case's date of *index diagnosis*. The majority of controls, will, however, never have had CRC (or CRA). In later stages of the evaluation, all incident cases will be considered (Design 4).

All cases and controls will appear on the HSCIC database at Exeter and will have available data on bowel, cervical (for women aged 60–64) and breast (for women aged 60–74) screening strictly prior to the date of *index/first diagnosis* of the case, depending on the analysis (that is, they have been invited to screening at least once prior, see Table 1 for details). Bowel, cervical and breast screening history as well as primary CRC pathology variables will be retrieved for all cases and controls. In addition, history of previous CRA and corresponding tumour pathology variables will be obtained.

A detailed description of the subject selection criteria and matching algorithm will be created in collaboration with our NHS partners.

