**Table 2 Tab2:** **Variables of interest for cases and controls**

Patient characteristics	Primary CRA & CRC pathology variables ^2^	Screening variables ^3^
Patient unique ID	Tumour unique ID	Screening Health Authority cipher (NHAIS)
NHS number	Tumour status	Screening office code
Sex	Tumour description	Screening office reference
Case or control	ICD-10 code	Year of first invitation to bowel cancer screening
	• C18 - Colon	
	• C19 - Rectosigmoid junction	
	• C20 - Rectum	
Date of birth	Dates of diagnoses (all CRAs & CRCs)	**For bowel/cervical/breast screening**
Patient status (Alive or dead at end of study period)^1^	Tumour detection mode (all CRAs & CRCs)	Episode number
Date of death (where applicable)	Anatomical subsite (all CRAs & CRCs)	Episode type
Age at death (where applicable)	CRC Dukes' stage (& any subsequent restaging)	Episode date
Date of *index tumour* diagnosis	CRA villousness	Screen date
Age at *index tumour* diagnosis	Tumour size (all CRAs & CRCs)	End code
Died of primary CRC (where applicable)	Treatment/procedure at diagnosis (all CRAs & CRCs)	Flag: NHS or Screening Programme registration by age 60
Cancer registry	Any further treatment/procedure (all CRAs & CRCs)	
Geographical area (as available in NCDR)	*Optional:* Dates of treatment (all CRAs & CRCs)	
IMD quintile (or postcode)		
Ethnicity		

^1^For cases and controls who died after date of *index diagnosis* of the case.

^2^Those variables will be retrieved for each neoplasia occurrence.

^3^All screening history.

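### Stratifying time since last screen by tumour detection mode, and the optional stage adjustment, do not give usable screening effects in the matched analysis

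*Protocol article*

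**What the plan says.** All case–control "analyses will be conducted using conditional logistic regression" (Statistical methods). The paragraph on secondary analyses has two relevant statements.

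- It opens "Secondary analyses will consider time since last screen stratified by age at diagnosis/pseudo-diagnosis, by" and continues with the index/first tumour's "detection mode, and by region (Main phase only"). This is a commitment.
- It then says "Analysis may be adjusted for stage at diagnosis". This is an option.

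Table 1 defines the cases of Designs 1 to 3 as Duke B or worse at index diagnosis and leaves the index-diagnosis cell for controls empty. Its analysis rows for Designs 1 and 2 include "Adjusting for screen-detection of CRC". The text after Table 1 says "Matched general population controls will be restricted to those individuals who have never had stage B or worse primary CRC". It lets controls have an earlier Duke A cancer or an adenoma, but expects most to have had neither. Table 2 lists "Tumour detection mode (all CRAs & CRCs") among the variables to be retrieved.

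The section on exposure opportunity bias states that a screen-detected case always has its detection screen on record, while most controls have no corresponding screen. It also warns that simply removing detection screens would bias the result in favour of screening.

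**The concern.** Both variables describe a tumour, and the comparison is between people with an index tumour and people without one.

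In Designs 1 to 3 stage is part of what makes someone a case, and it is also what screening is meant to change. It cannot act as a confounder within a matched set.

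Detection mode is a consequence of exposure: a person who was never screened cannot be screen-detected. Since most controls have no tumour, the natural reading is that each matched set is placed by its case's detection mode. The cases are then sorted partly on their exposure, and the controls are not.

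The protocol wants time since last screen to indicate the benefit of screening at different intervals, including the two-year programme interval. Screen-detected cases sit at the shortest interval, so that is where most of the distortion would fall.

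**Working it through.** **Stage, Designs 1 to 3.** There are two ways to enter stage as a covariate.

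1. *Each person's own stage.* Every case is Duke B or worse; every control has no stage or, rarely, Duke A. Stage separates case from control within the set, so its coefficient has no finite estimate and nothing is left to estimate the screening effect. In a simulation of 2,157 matched pairs (3 × 719) with the Table 3 probabilities, the unadjusted odds ratio was 0.84, with a standard error of 0.07 on the log scale. Adding individual stage raised that standard error to 8.85. Giving 0.3% of controls Duke A did not help (20.4).
2. *The case's stage assigned to the whole set.* The term is constant within sets and cancels from the conditional likelihood. In the simulation the information matrix could not be inverted.

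Splitting the same simulated sets by the case's stage gave finite odds ratios of 0.79, 0.87 and 0.86. Stage was generated independently of exposure, so these show only that the analysis works.

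**Detection mode.** Inputs from Table 3, per 100 case–control pairs: both screened 39, case only 16, control only 20, neither 25. Screened cases are 39 + 16 = 55. The plan's own odds ratio is reproduced: 16/20 = 0.80.

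Let s be the percentage of all cases that are screen-detected. The documents do not give it, so a range is assumed. All of these cases are screened. Assume also that their controls are screened as often as the controls of other screened cases. Then:

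- Screen-detected stratum: case-only pairs = 16 × s/55; control-only pairs = 0; the ever-screened odds ratio is not finite.
- Remaining stratum: case-only pairs = 16 × (1 − s/55); control-only pairs = 20; odds ratio = 0.80 × (1 − s/55).

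| s | Case-only pairs, screen-detected | Case-only pairs, remaining | Control-only pairs, remaining | Odds ratio, remaining |
|---|---|---|---|---|
| 5% | 1.45 | 14.55 | 20 | 0.73 |
| 10% | 2.91 | 13.09 | 20 | 0.65 |
| 20% | 5.82 | 10.18 | 20 | 0.51 |

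**With no effect at all.** Keep 36% of pairs discordant but split them equally, 18 and 18. Screened cases are then 39 + 18 = 57, and the remaining stratum gives 1 − s/57: 0.91, 0.82 and 0.65 for s = 5%, 10% and 20%. An apparent benefit arises from the split alone.

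**Designs 1 and 2.** If the adjustment is an indicator for a screen-detected index cancer, it equals 1 for some cases and 0 for controls. Its coefficient runs to infinity, the sets with a screen-detected case stop contributing, and the screening odds ratio comes from the remaining sets only. That is the last column of the table again.

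**The case against.** **The variables are not confined to cases.** This is right. A minority of controls may have Duke A cancer or an adenoma with stage or detection mode recorded. Nor does exposure fully determine detection mode, because a screened person can have an interval cancer. But no control has an index diagnosis, and the implication that matters, from screen-detected to screened, still holds.

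**Stage adjustment is optional and may mean separate analyses by stage.** On that reading the analysis is sound. However, the same section speaks of stratifying for sex and subsite and of adjusting for stage, and adjustment within this model fails under either coding. The point is limited to Designs 1 to 3; in Design 4 stage does not define the outcome.

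**The protocol already deals with screen-detected cases.** Design 5 compares them with controls screened in the same period, and the related sensitivity analysis excludes the index screen. An analytical correction and an extended pseudo-diagnosis date are also planned. These are good measures, but none is tied to the detection-mode stratification; Design 5 is presented as a further analysis. It also covers Duke A to D, so as tabulated it does not answer the advanced-disease question. The non-finite odds ratio does depend on counting the detection screen, which the stratified plan does not rule out.

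**The figures concern ever screened, not time since last screen.** This also stands. They illustrate direction and rough size, and are not predictions for the interval analysis.

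**Table 1 does not say whose screen-detection is adjusted for.** The line appears only in the two designs that admit an earlier Duke A cancer, so it could mean that earlier cancer. Some controls could then carry the variable and the estimate might be finite, but the model would still condition on a consequence of screening.

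**Conclusion.** The concern holds in limited form. In Designs 1 to 3 a stage covariate cannot adjust anything in the planned model. With the detection screen counted, the screen-detected stratum is degenerate, and the non-screen-detected stratum is biased in favour of screening for any screen-detected share above zero. In the ever-screened illustration, 0.80 becomes about 0.73, 0.65 or 0.51 at shares of 5%, 10% or 20%. This rests on the assumed shares, on Table 3's one-to-one pairs (the study will have two controls per case), and on screen-detected cases having controls like those of other screened cases.

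A reader might infer that stage and detection mode exist only for cases, that exposure fixes detection mode, and that all odds ratios involving them are undefined or biased. The documents do not support that. Some controls have these variables, interval cancers occur, analysis of matched sets by the case's stage is valid, and Design 5 is a coherent comparison. Nor does the secondary-analysis text affect the primary ever-screened estimate. The exception to watch is the screen-detection adjustment in Designs 1 and 2, which could reach the main analysis.

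**What to change.** 1. Replace the stage adjustment with separate matched analyses by the case's stage (B, C, D), keeping each case with its own controls.
2. For screen-detected cases, use controls screened in the same period and exclude the index screen, as in the Design 5 approach. Restrict this to Duke B or worse when advanced disease is the outcome.
3. Label any non-screen-detected stratum as descriptive, and state that it does not estimate screening benefit.
4. In Table 1, Designs 1 and 2, say which cancer the screen-detection adjustment refers to, and apply the same reasoning: remove it from the model for the screening effect, or report it as descriptive only.

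The cost is a few wording changes and a small amount of extra analysis on data already to be collected. The price in interpretation is that detection-mode strata can no longer be read as screening effects.

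### In the age-band secondary analysis the two outcome bands are transposed: as written, the pilot windows overlap at ages 62–64 and the main phase leaves ages 62–64 out

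*Protocol article*

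**What the plan says.** Among the secondary analyses in the Statistical methods section, the protocol article describes an age-band analysis modelled on the cervical screening audit. The exposure is given first for the pilot, "The effect of attending a screen in a particular 5-year age band (e.g. 60–64), in the pilot phase", and then for the main phase, a "2-year age band (e.g. 60–61), in the main phase". The outcome is advanced primary colorectal cancer "in the subsequent 5-year age band (i.e. 62–66 or 65–69, respectively").

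The exposure bands are offered as examples (*e.g.*). The outcome bands are introduced by *i.e.*, so they read as a definition.

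The article then gives a cross-check: "The results of this analysis should be very similar to those obtained from the analysis of" time since last screen, once that analysis is stratified by age at diagnosis or pseudo-diagnosis. Earlier in the same section, time since last screen is to include whether the last screen fell within the past two years, "as this corresponds to the NHS BCSP interval and approximates the estimated preclinical screen-detectable period (PCDP").

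**The concern.** *Respectively* ties the first outcome band (62–66) to the first exposure band (pilot, 60–64), and the second (65–69) to the second (main phase, 60–61). Neither pair fits the word *subsequent*.

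If the sentence is coded as it stands:

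- **Pilot.** A case diagnosed at 62, 63 or 64 is classified on an exposure band that is not yet complete at diagnosis. A screen that detects a cancer at those ages can also count as the exposure.
- **Main phase.** Cancers at 62–64, the years directly after the exposure band, are not analysed at all.
- **Cross-check.** The expected agreement with time since last screen is undermined, and a mismatch produced by the windows could be taken for a finding.

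The evaluation is meant to be repeated every two years, so the sentence may be implemented more than once.

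**Working it through.** **Inputs** (all from the Statistical methods section): exposure bands 60–64 (pilot) and 60–61 (main phase); outcome bands, in the order stated, 62–66 and 65–69; outcome described as the subsequent 5-year band.

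**Rule.** In whole years of age, the 5-year band that follows exposure band a–b is (b+1)–(b+5).

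- Pilot, b = 64: (64+1)–(64+5) = 65–69.
- Main phase, b = 61: (61+1)–(61+5) = 62–66.

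These are the two outcome bands that the article lists, in the opposite order.

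**Overlap, gap and time since a screen in the band.** Overlap is the set of ages in both bands. Gap is the set of ages between the end of exposure and the start of outcome. In exact age, a band a–b runs from a up to just under b+1. The time from a screen in the exposure band to a diagnosis in outcome band c–d therefore runs from c − (b+1) to (d+1) − a.

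| Pairing | Phase | Exposure | Outcome | Overlap | Gap | Time, years |
|---|---|---|---|---|---|---|
| As written | Pilot | 60–64 | 62–66 | 62, 63, 64 | none | 62 − 65 = −3 to 67 − 60 = 7 |
| As written | Main | 60–61 | 65–69 | none | 62, 63, 64 | 65 − 62 = 3 to 70 − 60 = 10 |
| Swapped | Pilot | 60–64 | 65–69 | none | none | 65 − 65 = 0 to 70 − 60 = 10 |
| Swapped | Main | 60–61 | 62–66 | none | none | 62 − 62 = 0 to 67 − 60 = 7 |

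**Reading the table.**

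- Pilot as written: 3 of 5 outcome years are also exposure years. The negative lower limit means that part of the exposure band lies after some of the diagnoses. Exposure counts only strictly before diagnosis (Study design & objectives), so for those subjects the band is cut short.
- Main phase as written: the shortest time from a screen in the band to a counted diagnosis is 3 years. That is longer than the two-year span singled out for time since last screen.
- Swapped: both pairs satisfy the rule exactly.

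**The case against.** **The intention is recoverable.** The operative word is *subsequent*, and it fixes both pairs without the bracket. Only one swap makes both phases fit, and a careful analyst would probably make it. This stands: it is a slip in wording, not a poor choice of method. It does not remove the point, because the bracket is written as a definition and contradicts the rule it is meant to spell out.

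**The analysis is secondary.** The primary measure is ever having attended a screen, and estimates of benefit at different intervals are assigned to time since last screen. The age-band analysis works largely as a parallel check. This also stands.

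**Stronger readings a reader might infer, which the article does not support:**

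- *The overlap creates a detection-screen bias that the plan has missed.* The Exposure opportunity (frequency) bias section already says that screen-detected cases carry their detection screen, and that this biases against screening. It plans an analytical correction and sensitivity analyses in which control dates "will be extended by up to 3 years, the estimated average sojourn time for each screen-detected case". Controls also take the matched case's date and are close to the case in birth date, so exposure at 62–64 is truncated almost equally in both groups. Nowhere does the article say that a later outcome band is there to prevent this bias. What remains is that the overlap lets detection screens at 62–64 into an exposure band that the adjacent pairing would largely keep clear of them.
- *The main phase would lose most of the benefit of screening.* Suppose a screen at exactly 61 and an exponential detectable period with mean m. The average of exp(−t/m) over t = 1 to 6 (ages 62–66) is m(e^(−1/m) − e^(−6/m))/5, which is 0.223 for m = 2 and 0.349 for m = 3. Over t = 4 to 9 (ages 65–69) it is 0.050 and 0.128. The relative falls are 78% and 63%. The means of 2 and 3 years come from the article, but the exponential form and the single screen do not. The figure is a share of cancers already detectable at one screen. It has no stage progression, test sensitivity or repeat invitation in it, so it illustrates direction only and is not an estimate of lost benefit.
- *Interval policy could be misled.* The article does not rest interval conclusions on this analysis alone, and a wrongly windowed result could show up as a disagreement with time since last screen.
- *The cross-check must fail.* People screened at 60–61 may be screened again before 65–69, so time since a screen in the band is not time since last screen. The literal pairing weakens the expected agreement; it does not make agreement impossible.

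**Conclusion.** The outcome bands are wrong as written. Read with *respectively*, the pilot has three years (62–64) that are both exposure and outcome. The main phase omits the same three years and starts counting diagnoses 3 years after its exposure band ends. Both contradict *subsequent* and sit badly with the expected similarity to time since last screen. These figures are exact and need no assumption beyond reading age bands as completed years.

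The reach is limited. This is a transposition in one secondary analysis, with an evident intended meaning. The primary odds ratio and the sample size do not depend on it. No size can be put on the resulting error in the odds ratio from the article; any percentage loss of benefit rests on an assumed sojourn distribution. The sentence should be corrected before the analysis is programmed.

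**What to change.** Drop *respectively* and write the two pairs out: in the pilot, a screen at 60–64 with advanced cancer at 65–69; in the main phase, a screen at 60–61 with advanced cancer at 62–66. Add that for every other exposure band the outcome band is the 5-year band starting at the next year of age, with no overlap and no gap.

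The cost is one sentence. No extra data, subjects or change to the primary analysis is needed.
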